#### Patient withdrawal

Patients in both groups can quit the study at any time point. Patients who withdraw from the study are asked whether they agree to continue to fill in a limited set of questionnaires related to the primary study outcome.

#### Physician encounters

It is aimed that patients do not see a neurologist during the coaching stage. However, there are situations where patients have to or want to see a neurologist (for example, for relapse management). In these cases, neurologists in the participating outpatient clinics and practises are asked whenever possible not to discuss immunotherapy options. Still, this might not always be appropriate and some patients might also consult a practice-based neurologist. Any physician encounter will be documented.

### Strategies to improve adherence

#### Decision coaches

All decision coaches will receive a study coach folder including all relevant documents of the training, the patient workbooks, moderation cards, and further material on communication and coaching.

Coaching fidelity will be secured through different measures: first, an interactive three-day training course in Hamburg; and second, video feedback of two coaching patients per nurse in the respective centre. Also, they will be contacted regularly (monthly during the first three months and every two to three months afterwards) to ensure quality standards of coaching sessions and support the decision coaches. Calls will consist of open and closed questions and decision coaches will have the opportunity to come up with their own aspects (as for example questions concerning coaching procedures or the DECIMS-Wiki). Furthermore, we aim to hold three to four telephone conferences per year with participating nurses from the IG. This will provide an opportunity for the nurses to connect and share experiences, for example to discuss difficult coaching situations.

#### Logbook

Decision coaches are further asked to use an online logbook for each participant to support a standardised delivery of the intervention.

#### Coaching sessions

Moderation cards will be provided to decision coaches to ensure that the key components of the intervention are delivered to the patients. This adds to the patient workbook, which also provides guidance through the SDM steps. Coaches might prepare sessions by looking into the coaching cards. In each coaching session it is aimed that the DECIMS-Wiki, the moderation cards, and the patient workbook are used. Moreover, the workbook and the moderation cards do serve as structuring aids for the encounters.

#### Strategies to facilitate the utilisation of the DECIMS-Wiki

Decision coaches will be informed about the DECIMS-Wiki and use the tool during the training course, and the DECIMS-Wiki will be addressed during telephone calls and in the logbook. Beyond that, decision coaches will be informed when the platform has been updated.

### Patients

If patients miss an appointment, they will be contacted by the decision coach to arrange a new appointment. Patients will be contacted by email by a member of the coordinating centre in Hamburg when it is time to fill in a form, and will be asked to complete the questionnaires within a specified time period. Patients who miss the completion will again be reminded by email and telephone. When appropriate, patients will be asked to fill in a questionnaire in the outpatient clinic directly after an encounter.

Decision coaches will inform patients about the DECIMS-Wiki and use the tool during the first coaching sessions reminding patients to use it between sessions. All patients will receive a personal password for the DECIMS-Wiki and an information leaflet about the tool.

### Relevant concomitant care

#### Relapse management

In case of deterioration, for example a relapse during the coaching stage, the participant is free to consult a specialist and receive appropriate treatment.

### Outcomes

For a list of the major endpoints of the DECIMS trial, see Table 1.

**Table 1 Tab1:** **Major endpoints CRCT**

**Instrument**		**Measurement time points**						
		**Enrolment**	**Allocation**	**Post-allocation**				
		**-t** _**1**_	**t** _**0**_	**t** _**1**_	**t** _**2**_	**t** _**3**_	**t** _**4**_	**t** _**5**_
Eligibility screen		X						
Informed consent		X						
Allocation								
Sociodemographic data		X	X					
EDSS			X					
SDMT			X					
MS-related data and resource use			X				X	X
MMIC:								
	Risk knowledge		X			X	X	X
	Attitude			X	X	X		
	Immunotherapy status		X			X	X	X
Dyadic DCS				X (nurse)	X (physician and patient)			
Dyadic MAPPIN’SDM				X (nurse and patient)	X (physician and patient)			
HCR trust scale (Physician/Nurse trust)				X	X			
PBMS			X			X		X
CPS			X			X		X
Decision autonomy						X	X	X
CSES			X			X		X
HAQUAMS			X			X		X
HADS			X			X		X

t_1_ = after last decision coaching; t_2_ = directly after final physician decision encounter; t_3_ = two weeks after final physician encounter; t_4_ = three months after final physician encounter; t_5_ = six months after final physician encounter. CPS: Control Preference Scale; CSES: Coping self-efficacy scale; DCS: Decisional Conflict Scale; EDSS: Expanded Disability Status Scale; HADS: Hospital Anxiety and Depression Scale; HAQUAMS: Hamburg Quality of Life in MS Scale; HCR trust scale: Health care relationship trust scale; MAPPIN’SDM: Multifocal Approach to Sharing in Shared Decision Making; MMIC: Multi-dimensional measure of informed choice; MS: Multiple Sclerosis; PBMS: Planned Behaviour in MS Scale; SDMT: Symbol Digital Modalities Test.

### Primary outcome

We have previously applied the multi-dimensional measure of informed choice in two controlled trials [52]. Here, informed choice is defined as a compound measure combining three dichotomous measures: risk knowledge, attitude, and therapy uptake. Informed choice encompasses adequate risk knowledge, with either uptake or non-uptake of immunotherapy, and a corresponding (congruent) positive or negative attitude. Attitude will be assessed using a single question directly after the final physician encounter. Uptake will be evaluated from the patient after six months. Risk knowledge will be measured using a previously developed and adapted questionnaire 14 days, and three and six months after the last physician encounter [53]. As applied in a previous trial, the cut off for adequate risk knowledge will be defined *a priori* as the value that 30% of all patients with highest scores reach at baseline. In addition, risk knowledge will be analysed as a continuous variable to enable comparability with other studies. Earlier trials have shown that patients who meet the primary endpoint more often realise their preferences [38,39].

### Secondary outcomes

The Decisional Conflict Scale ((DCS) [54]) has been used in numerous decision support interventions and is regarded as a tool to monitor comfort with the decision process. Here, a dyadic DCS [55] (patient - decision coach and patient - physician) will be applied as key secondary endpoint after the last coaching session (IG) and after the final physician encounter (for both the IG and CG).

Further tools will be used to monitor decisional processes assessing autonomy preferences (Control Preference Scale (CPS) [56]), behavioural beliefs, and self-efficacy (Planned Behaviour in MS Scale (PBMS) [57]). Coping and self-efficacy will be assessed by application of the recently validated Coping Self-efficacy Scale (unpublished data [name], [name], [name], [name], [name]) based on Chesney *et al*. [58]). Perceived involvement in coaching and decisional encounters from patients’ as well as physicians’ and nurses’ perspectives will be evaluated with the Multifocal Approach to Sharing in Shared Decision Making (MAPPIN’SDM) evaluation [59]; applying a newly developed short version. We will assess participants’ trust in nurses and physicians [60].

Decisional adherence (including the decision against immunotherapy) and acceptance of the intervention will be assessed from patients using a standardised questionnaire at three and six months after the last physician encounter (for both the IG and CG). Finally, duration of decision coaching and physician encounters will be documented.

### Tertiary outcomes (control and safety parameters)

As control parameters we will use measures for anxiety and depression using the Hospital Anxiety and Depression Scale ((HADS) [61]), and disease-specific quality of life using the Hamburg Quality of Life in MS Scale ((HAQUAMS) [62]). Moreover, standard disease-monitoring parameters will be obtained; relapses and disability as measured by Expanded Disability Status Scale ((EDSS) [63]) and the Symbol Digital Modalities Test ((SDMT) [64]) for cognition. Occurrence of relapses will be evaluated at baseline, 14 days, and three and six months after the last physician encounter (for both the IG and CG) using a standardised questionnaire.

### Health economic outcomes

Data to perform health economic analyses will be assessed with an adapted tool used in a previous trial [35]. Patients will be asked to consent for collection of health insurance data for the study period.

Focus will be the rate of patients initiating MS immunotherapy as well as relapse treatment prescription (including route of administration). Further, number of MS-related visits to neurologists and general physicians, number of MRI scans, missed days at work, and hospital stays will be evaluated.

### Participant timeline

For a description of the flow of the DECIMS trial see Figure 2.

**Figure 2 Fig2:**
[figure not shown]
**DEcision Coaching In persons with relapsing-remitting Multiple Sclerosis (DECIMS) trial flow.**

CRCT: cluster randomised controlled trial; DCS: Decisional Conflict Scale; MAPPIN'SDM: Multifocal Approach to Sharing in Shared Decision Making; MMIC: Multi-dimensional measure of informed choice RRMS: relapsing-remitting multiple sclerosis

### Screening visit

As it is not possible to coach all suitable patients in every participating centre, not all potentially eligible patients will be included. To avoid selection bias, possible recruitment days will be randomly determined by a statistician for those centres, and an independent person will call the study sites weekly to inform them about the recruitment day(s).

Nurses (for both the IG and CG) will create a list on all recruitment days, recording all MS patients who attend the outpatient clinic that day. Potentially eligible patients will be identified using a screening form (form one) during an appointment. Screening form one has to be filled in for every patient. Therefore, reasons why patients are not suitable will be documented as well. When patients seem to be suitable for the study, they will receive information about the study from the physician or from a nurse. For diagnostic cases in which an early treatment will be discussed, physicians will invite patients after having communicated diagnostic test findings. In the case of treatment switchers, the encounter is stopped before counselling about the possible immunotherapy options will take place. Physicians have to fill in a second screening form, including the study inclusion criteria, for all patients who seem to be suitable for the study. Informed consent will be obtained from patients fulfilling the inclusion criteria after they have had enough time to read the study information sheet and ask questions. The encounter will be stopped when informed consent is given, and patients will be invited to fill-in baseline data via an online questionnaire database and will receive an access code to the DECIMS-Wiki after the completion of baseline questionnaires. Depending on the cluster’s group allocation, patients will receive a new appointment with the physician or an appointment with the decision coach. Suitable patients, who are not willing to participate in the study, will be asked for the reason (screening form two).

### Baseline data and allocation

After information about group allocation, patients in the CG will receive an information sheet about the DECIMS-Wiki from a nurse, will receive usual care, and a decisional encounter with the physician will be scheduled. In the IG, apart from information about access to the DECIMS-Wiki, an appointment for a first encounter with the decision coach will be scheduled within 14 days. After inclusion and the completion of baseline questionnaires, patients will receive an electronic access code to the DECIMS-Wiki, which is linked to the information technology platform of the *Krankheitsbezogenes Kompetenznetz Multiple Sklerose* ((KKNMS) Competence Network Multiple Sclerosis). Further appointments will be planned at the end of each encounter, which could be up to two more with the decision coach and up to two with a physician.

### Encounters and web-based visits

After the last encounter with the decision coach, prompt feedback from patients will be collected at the centre by web-based questionnaires. After up to three meetings with the decision coach (visits one to three), up to two decisional encounters with a physician will take place within four weeks. Decision coach encounters will be videotaped and sent to the Hamburg study centre for analysis by the research group.

Patients will be followed up on using web-based questionnaires within 14 days, after the final encounter with the physician (web-based visit), after three months (web-based visit), and after six months (web-based visit and standardised telephone interview).

### Additional visits

At least three randomly selected patients from each intervention cluster will be contacted after the follow-up period and asked to take part in an additional interview, which will be conducted in the context of the accompanying process evaluation (for details see process evaluation). Furthermore, when additional funding is provided, patients will be contacted via telephone by the study centre to assess their current treatment status after 12 and 24 months.

### Sample size

The primary endpoint of the DECIMS trial is informed choice, that is, a fitting of good knowledge, a given attitude, and the corresponding uptake. Each of these three dimensions will get a dichotomous rating of ‘yes’ or ‘no’. Based on data from prior studies [35,36], we assume that after the intervention, 60% of patients in the IG will show ‘adequate’ knowledge compared to 40% in the CG. Adequate knowledge is defined as the number of questions correctly answered by 30% of patients at baseline, which was also applied in previous work. We assume that in the IG group about 80% of attitudes and decisions are congruent, compared to 70% in the CG. Therefore, we expect 48% of IG patients to make informed decisions compared to 28% of patients in the CG. In order to detect this difference with a power of 90% and a significance level of alpha = 0.05, 12 clusters with 23 patients per cluster will be needed, assuming an intra-cluster correlation coefficient of 0.0045, which is a conservative estimate based on data from our previous trial [38].

Assuming a dropout rate of 10%, 25 participants per centre will be needed, accounting for a total of 300 participants in 12 clusters. In all our previous trials on EBPI, loss to follow-up was less than 10%. Therefore, 10% seems a realistic and conservative assumption.

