### Statistical methods

For the primary outcome measure, the proportion of informed decisions within a treatment group, a generalised linear mixed model, reflecting the hierarchical structure of the data will be used [65]. Due to the relatively small numbers of clusters, imbalances in baseline characteristics on cluster and individual level may occur which are not fully covered by randomisation. Therefore the model will be adjusted for baseline variables. The treatment effect will be analysed at cluster level, whereas covariates will be analysed individually by the model. For the secondary outcome measures linear mixed models or generalised linear mixed methods will be used adjusting for clusters by random effects. These models also allow analyses of subgroups. All analyses will be performed on the intention-to-treat population.

It is planned to perform subgroup analysis of the two groups of patients included in the trial: first, those with a recent diagnosis, facing an initial decision on immunotherapy and second, those considering changing to an oral treatment. Apart from demographic baseline data, all analyses will be cluster-adjusted. We will report causes for study withdrawal for each patient to clarify whether there are any differences between the intervention and control clusters.

In addition, a sensitivity analysis will be performed to evaluate the robustness of study results and to explore different imputation techniques. Altman [66] addressed that there is no ideal method to address missing data. Therefore, different common imputation techniques [67] will be applied and reported with as well as without imputation techniques as suggested by Altman [66]. Last observation carried forward, as well as best and worst case scenario for dichotomous outcomes and multiple imputation techniques, will be conducted in the sensitivity analysis [68].

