### Context

Relevant factors of the German health system will be described and their relevance for this project will be discussed. A total of 14 different MS outpatient clinics are involved in the study, nine related to university hospitals and five to community based hospitals. Depending on the location, there is significant variation between the outpatient clinics, and due to factors such as size, practice hours, and clinical focus of the clinics, the number of potential study participants vary considerably. In the planning phase of the study, participating centres were visited in order to gain important information about structure and processes within the outpatient clinics. Based on the evaluation of this information, the conduct of the study and process evaluation content was adapted.

Patient populations of the different outpatients clinics consist of patients who:recently received a diagnosis and require information about therapy options,visit the outpatient clinic regularly and now face a treatment decision (start, stop, or change of immunotherapy),seek a second opinion, and/orother (for example acute relapse).

Accordingly, the staffing (doctors, study nurses, MS nurses, and receptionists) and the roles of outpatient clinics in the respective neurological department are organised differently. Similarly, the clinics differ in terms of everyday processes, the functions assumed (by doctors and nurses) in patient care, and patient populations. Many of these differences have been noticed during the visits. As a result, the analyses of these different contextual conditions will provide important information concerning transferability of the concept to MS outpatient clinics in Germany, and to other countries and medical fields.

Prior to randomisation of the centres, study contextual factors will be assessed in a baseline survey (self-developed questionnaire (for both the IG and CG)). In addition, certain aspects of possible centre-specific effects (promoting factors and barriers) will be explored in more detail after completion of the study through qualitative interviews. For example, the possible advantages and disadvantages of the team structure (such as number and qualification of employees) for the work of decision coaches will be studied by qualitative interviews.

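### The stated 90% power holds only for a Wald z test with a true ICC of about 0.0045 or less; on cluster-level degrees of freedom it is about 83–85%, and the ICC should not be called conservative

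*Protocol article*

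**What the plan says.** All references are to the protocol article.

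- **Sample size, effect and error rates.** For the primary outcome, "we expect 48% of IG patients to make informed decisions compared to 28% of patients in the CG". The difference is to be detected "with a power of 90% and a significance level of alpha = 0.05". Sidedness is not stated.
- **Sample size, clusters and ICC.** "12 clusters with 23 patients per cluster will be needed, assuming an intra-cluster correlation coefficient of 0.0045, which is a conservative estimate". The source is one earlier trial. The Background describes it as a multicentre study of 192 patients with early MS that compared group education with stress management. Its number of centres is not given.
- **Sample size, dropout.** "Assuming a dropout rate of 10%, 25 participants per centre will be needed, accounting for a total of 300 participants in 12 clusters".
- **Statistical methods.** The primary analysis is a generalised linear mixed model that reflects the hierarchical structure. "The treatment effect will be analysed at cluster level, whereas covariates will be analysed individually by the model". The section concedes that there are few clusters, but uses this only to justify adjustment for baseline variables.
- **Allocation.** Clusters are stratified by hospital type, with two strata.

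**The concern.** With 12 randomised clusters, a treatment effect tested against between-cluster variation has about 10 degrees of freedom. Its critical value is then 2.228, not 1.960. A power figure from the normal formula does not describe that test. The Statistical methods section places the treatment effect at cluster level, so the power paragraph and the analysis paragraph may refer to different tests.

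The result is also sensitive to the ICC. The value used is close to zero, comes from one modest trial of a different intervention, and is presented as erring on the safe side with no interval or range.

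At stake is how a neutral result is read. A type II error rate of 10% is advertised. On cluster-level degrees of freedom it is about 15–17% at the plan's own ICC, and about 26–28% at an ICC of 0.02 with 22.5 analysed per cluster.

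**Working it through.** **Inputs.** From Sample size: 48% v 28%, alpha 0.05, 12 clusters, m = 23 analysed per cluster, ICC 0.0045, 10% dropout, 25 recruited per centre. From Allocation: two strata. Assumed: two-sided test, 6 v 6 clusters, equal cluster sizes.

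**1. Reproduce the plan's figure.**
- Unpooled variance: 0.48 × 0.52 + 0.28 × 0.72 = 0.4512. Pooled: 2 × 0.38 × 0.62 = 0.4712.
- Patients per arm without clustering: (1.960 + 1.282)² × 0.4512 / 0.20² = 118.5. With the pooled variance under the null it is 121.7, so 122.
- Solving 6m = 122 × [1 + (m − 1) × 0.0045] gives m = 22.3, so 23.
- At m = 23 the design effect is 1 + 22 × 0.0045 = 1.099. The effective number per arm is 138 / 1.099 = 125.6, and normal-theory power is 90.9% (pooled null) or 91.6% (unpooled).

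The figure therefore reproduces. A continuity-corrected formula needs m = 24.3, so 25, and one-sided 0.05 gives 95.1%; neither matches. The protocol names no formula, so the absence of a small-sample allowance is inferred from this match.

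**2. Same inputs on cluster-level degrees of freedom.** SE = √(variance × design effect / 6m).
- Unpooled, m = 23: √(0.4512 × 1.099 / 138) = 0.0599, so the noncentrality is 0.20 / 0.0599 = 3.34. Pooled: 0.0613 and 3.26.
- Noncentral t power at ICC 0.0045 (pooled to unpooled variance):

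| Analysed per cluster | 10 df | 9 df (stratum fitted) |
|---|---|---|
| 23 | 83.6–85.2% | 82.7–84.3% |
| 22.5 (25 less 10%) | 82.9–84.5% | 82.0–83.6% |
| 25 (no dropout) | 86.2–87.7% | 85.4–86.8% |

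Simulated t-tests on beta-binomial cluster proportions (6 v 6, m = 23) gave about 84.5%. About 14 clusters of 23 would be needed for 90% on this test.

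**3. The mixed model with a Wald z test.** A random-intercept logistic model was fitted to simulated clusters of 23:
- ICC 0.0045: type I error about 4.6–5.2%, power about 90–91%.
- ICC 0.01: type I error about 6%.
- ICC 0.02: type I error about 7.5–8.5%.

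With a t(10) critical value, the same model at ICC 0.0045 had type I error of 2.4–2.6% and power of about 85%.

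**4. Sensitivity to the ICC.** The values 0.01, 0.02 and 0.05 are assumed; the documents give no other ICC. With 22.5 per cluster and 10 df:

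| ICC | Design effect | Power |
|---|---|---|
| 0.01 | 1.215 | 79.0–80.7% |
| 0.02 | 1.430 | 72.3–74.2% |
| 0.05 | 2.075 | 56.4–58.3% |

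The normal formula at 22.5 per cluster also falls below 90%: 87.2–88.1% at ICC 0.01 and 81.3–82.5% at 0.02.

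**5. What 192 patients can say about an ICC of 0.0045.** SE = (1 − r)(1 + (m − 1)r)√(2 / [m(m − 1)(k − 1)]) with k centres and km = 192. Taking k from 4 to 12 (an assumption), the SE is 0.021–0.029. That gives a Wald upper 95% limit of about 0.045–0.062. F-based limits are wider, about 0.12–0.25.

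**6. Dropout line.** 25 × 0.9 = 22.5 per centre, or 270 in total, against the 23 (276) stated as needed. 23 / 0.9 = 25.6, so 26.

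**The case against.** The strongest reply is that the planned analysis is a mixed model on patient data. The protocol names no t-test and no degrees-of-freedom rule, and that choice commonly sits in an analysis plan. The sentence about cluster level may mean only that treatment is a cluster-level term. At ICC 0.0045 the Wald z test keeps its size and has about 90% power, while t(10) is too cautious because the between-cluster variance is often estimated as zero. This stands. A reader might infer that the design cannot exceed 84–85%, or that the sample-size arithmetic is wrong. The documents support neither: the arithmetic is right for its formula, the lower figure belongs to one class of test, and with all 25 per centre retained that test reaches about 85–88%.

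The reply does not rescue the unqualified claim. The z test keeps its error rate only near the assumed ICC, so the stated pairing of power and alpha depends on that one value.

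On the ICC, the protocol says the value is based on earlier data. It does not say that it is the raw point estimate, so it may already have been rounded up. The standard errors above also rest on an assumed number of centres. Both points are fair. They limit what can be said about the true ICC, but they do not supply evidence for calling it conservative.

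A reader might also take the Context section's remark that "there is significant variation between the outpatient clinics" as proof of a larger ICC. That passage concerns size, practice hours, clinical focus and numbers of potential participants, not informed choice, so it is no direct evidence about this ICC.

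On dropout, the unrounded requirement is 22.3, which 22.5 meets, and the plan reports loss below 10% in its earlier trials. This is a rounding inconsistency. Baseline adjustment could recover some power and unequal cluster sizes could cost some; the documents quantify neither.

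**Conclusion.** The concern holds in a limited form, at moderate severity. The 90% figure is conditional on two things that the Sample size section does not state: a Wald z test in the mixed model, and a true ICC of about 0.0045 or less. For a test on cluster-level degrees of freedom, which the Statistical methods wording suggests without fixing it, power at that ICC is about 83–85% with 23 analysed per cluster and about 82–84.5% with 22.5. This rests on a two-sided test, 6 v 6 clusters and equal cluster sizes.

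The loss is moderate at an ICC of 0.01 and large from 0.02 upwards. Those ICCs are illustrative: the documents do not show that the true value is that high, only that one 192-patient trial gives no basis for calling 0.0045 conservative. The dropout mismatch is minor.

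**What to change.** Leave 12 clusters and 300 patients unchanged, and revise the Sample size section:

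1. State which test the power refers to, and make it the same as the test of the primary treatment effect.
2. Restate power as about 83–85% for a test on cluster-level degrees of freedom at ICC 0.0045, and about 90% only for a Wald z test at an ICC of 0.0045 or less.
3. Delete the word conservative. Add power at ICC 0.01, 0.02 and 0.05, labelled as assumed values.
4. State that 25 per centre with 10% dropout leaves 22.5 evaluable, and that 26 would be needed for 23.

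The cost is a rewritten paragraph and a less favourable stated power. Recruitment, the intervention and the choice of model are unaffected.
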